### Statistical methods

Linear mixed models with random effects (participants) and an intention-to-treat approach will be used to evaluate within-group and between-group changes by time. All linear mixed models will allow for heterogeneity of variance according to study date and employ restricted maximum likelihood estimations. An α of 0.05 will be adopted for all analyses.

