#### Physical assessments

Both anthropometry and physical capacity (muscle flexibility, strength and power) will be quantified at baseline only. Outcomes will facilitate safety regarding exercise prescription and serve as potential confounding factors in statistical analyses. The following measures will be obtained using standard techniques: body mass, height, blood pressure, sit and reach,^65^ max single-leg calf raise,^66^ 30-second single-leg sit to stand,^67^ triple hop for distance^68^ (online supplemental appendix C).

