### Sample size

In line with recommendations,^69^ the current study was designed to detect the smallest effect size of interest between the intervention and control for each primary outcome (IVD T2, pain intensity and disability) at 12 week follow-up assuming an α of 0.05, β of 0.8 and adjustment for test–retest reliability.^70^ To detect a between-group net difference in IVD T2 of d=0.183 based on a minimum detectable change of 5.1 ms,^30^ SD of 27.9 ms^30^ and test–retest reliability of r=0.97,^30^ 28 total participants are required (n=14 per group). To detect a between-group net difference in pain intensity of d=1.00 based on a clinically meaningful change of 20 mm,^34^ SD of 20 mm^71^ and the most conservative test–retest reliability of r=0.57,^35^ 16 total participants are required (n=8 per group). To detect a between-group net difference in disability of d=0.52 based on a clinically meaningful change of 10 points,^72^ SD of 19.2 points^73^ and test–retest reliability of r=0.83,^72^ 20 total participants are required (n=10 per group). To account for a conservative attrition rate of 30%, despite retaining 80% of CLBP participants throughout our previous 6 month randomised controlled trial,^10^ 40 total participants (n=20 per group) will be recruited to detect the three primary outcomes smallest effect estimates of interest. All power calculations were conducted using G*Power (V.3.1.9.7).^74^

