### Allocation

Participants will be randomly assigned (1:1) using block randomisation with random block lengths (between 2 and 6 per block) and stratification for sex to either intervention or waitlist control. A team member without contact with participants will obtain and employ the randomisation schedule (creating sequentially numbered, opaque, sealed envelopes). The randomisation schedule will be developed using the ‘blockrand’ package in R V.4.1.2 (https://www.r-project.org/).^75^

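### The stated mixed model does not fix how baseline is used or name the sex stratum, while physical measures are offered as confounders; baseline adjustment would add precision, mainly for pain, at almost no cost

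*Protocol article*

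**What the plan says.** The primary analysis is given in the Statistical methods section: "Linear mixed models with random effects (participants) and an intention-to-treat approach will be used to evaluate within-group and between-group changes by time". That section adds restricted maximum likelihood and variances that may differ by study date, and closes with "An α of 0.05 will be adopted for all analyses". It lists no fixed covariate. Baseline adjustment is neither included nor excluded, and sex is not mentioned.

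The Allocation section says participants are assigned 1:1 "using block randomisation with random block lengths (between 2 and 6 per block) and stratification for sex".

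The Physical assessments section says that the baseline anthropometric and physical-capacity results will help make exercise prescription safe and will "serve as potential confounding factors in statistical analyses". Seven measures follow: body mass, height, blood pressure and four performance tests. The section does not say which of them would be used, in which model or by what rule.

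The Blinding section keeps the statistical analyses blinded to allocation until the planned analyses are finished.

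**The concern.** Every participant is due to have a baseline value of each primary outcome, since the schedule collects all three before follow-up. A group-by-time model with free baseline means uses that value only by subtraction. When baseline and follow-up are imperfectly correlated, subtraction carries baseline noise into the treatment contrast, whereas regression on baseline, or constraining the group means to be equal at baseline, does not. In a trial of 40 people that precision is worth having.

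Two further points bear on the same model. The one factor that governed allocation, sex, is not named in it. The factors that are offered for adjustment did not govern allocation and are described as confounders. In a randomised comparison a baseline imbalance is a chance event, so the reason to adjust is prognostic value, decided in advance. As worded, the clause leaves open whether and how these measures enter the primary estimate.

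**Working it through.** **The plan's own figures.** The Sample size section gives totals of 28 (T2), 16 (pain) and 20 (disability), "assuming an α of 0.05, β of 0.8 and adjustment for test–retest reliability". I read the 0.8 as power. The attrition step reproduces: 28 / (1 − 0.30) = 40. The three component totals do not reproduce with standard two-sided formulas: a change-score comparison needs 60 / 30 / 42, and a baseline-adjusted one 58 / 24 / 40. That is a separate matter, noted here only because the power figures below come from the standard formulas and not from the plan's totals.

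**Inputs (Sample size section).**
- T2: d = 5.1 / 27.9 = 0.183, r = 0.97
- Pain: d = 20 / 20 = 1.00, r = 0.57
- Disability: d = 10 / 19.2 = 0.521, r = 0.83
- 30% attrition from 20 per group leaves 14 per group
- α = 0.05, taken as two-sided because the plan does not say

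**Assumption.** r is test–retest reliability. I use it as the correlation between baseline and week 12, for which the document gives no figure.

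**Variance ratio.** With complete data, the contrast from free group-by-visit means is the difference in mean change, with variance proportional to 2(1 − r). The baseline-adjusted contrast has variance proportional to 1 − r². The ratio is 2(1 − r) / (1 − r²) = 2 / (1 + r).
- Pain: 2 / 1.57 = 1.274
- Disability: 2 / 1.83 = 1.093
- T2: 2 / 1.97 = 1.015

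**Sensitivity to r for pain.** The Pain intensity section quotes an ICC of 0.90 for the same scale: 2 / 1.90 = 1.05. If the 12-week correlation is lower than short-term reliability, the ratio is 1.33 at r = 0.5 and 1.54 at r = 0.3. The excess variance for pain therefore runs from about 5% to 54%.

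**Power.** Noncentral t with 2n − 2 degrees of freedom and noncentrality d·√(n/2) / √v, where v = 2(1 − r) for change and 1 − r² for adjusted. At n = 14, √(n/2) = 2.646.

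| Outcome | v, change | v, adjusted | Power at 14 per group | Power at 20 per group |
|---|---|---|---|---|
| Pain | 0.860 | 0.675 | 78% → 87% | 91% → 96% |
| Disability | 0.340 | 0.311 | 62% → 66% | 79% → 82% |
| T2 | 0.060 | 0.059 | 48% → 48% | 63% → 64% |

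**Simulation check.** With complete data at 20 per group, the standard errors for change, baseline-adjusted and constrained-baseline analyses were 5.78, 5.19 and 5.11 for pain; 3.52, 3.41 and 3.45 for disability; and 2.17, 2.18 and 2.19 for T2. The constrained version is about as precise as the adjusted one, and T2 shows no gain.

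**Sex.** The document gives no size for a sex effect. If sex explained an assumed 0 to 10% of residual variance, omitting it would inflate variance by up to 1 / (1 − 0.10) = 1.11, that is 0 to 11%. This applies only where the model is baseline-adjusted or constrained. In an unconstrained change contrast a sex main effect is the same at every visit and cancels.

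**The case against.** The strongest objection is that the Statistical methods section is a three-sentence summary in a journal article. A reader might infer that the plan rules out baseline adjustment and leaves sex out of the model. The text does not support that: it lists no covariates at all, its wording is compatible with a constrained-baseline mixed model, and a fuller analysis plan may exist. What stands is narrower. The article does state a model, its usual reading is the less precise one, and a better version costs nothing.

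A reader might also infer that seven measures open 128 adjustment sets (2⁷) from which a favourable one could be picked, biasing the result. The document does not show this. It does not say that measures will be chosen after seeing the data, it does not tie them to the primary model, and the blinded analysis limits any choice that favours an arm. Prespecified adjustment for prognostic baseline measures is legitimate. What remains is an inapt label and no stated rule.

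The size can be challenged too. The pain r of 0.57 is described as the most conservative available, and at 0.90 the excess is only 5%. The power figures treat dropouts as contributing nothing, whereas a mixed model would use their week 6 data where present. Both points are fair, so the figures are indicative. Finally, leaving out a prognostic stratum makes intervals too wide; it does not produce false positives.

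**Conclusion.** The point holds as an inexpensive improvement to a stated but incompletely fixed model, and not as proof of a wrong analysis. On the free-baseline reading, the loss against baseline adjustment is material for pain (about 27% more variance, plausible range 5% to 54%), modest for disability (about 9%) and negligible for T2 (1.5%). For pain at the planned attrition, it is the difference between falling just short of 80% power and clearing it.

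A reader might hope that the change would also rescue T2, the outcome that sets the sample size. It would not: power stays at about 48% with 14 per group. The cost of leaving sex out cannot be sized from the document.

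These conclusions rest on test–retest reliability standing in for the 12-week correlation, two-sided testing at 0.05, and complete data at the stated numbers.

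**What to change.** In Statistical methods, state for each primary outcome one of two models. The first is a linear mixed model with weeks 6 and 12 as responses, group, visit and group-by-visit terms, and the baseline outcome as a covariate with its own slope at each visit. The second has all three visits as responses and baseline means constrained equal across groups; it also keeps in the model participants who have only a baseline value. In either, include sex as a fixed effect, since a sex main effect helps only in a model of this kind.

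In Physical assessments, drop the confounder clause as far as the primary analysis is concerned, or name in advance any measure to be used and confine it to a sensitivity analysis.

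The cost is wording and one or two degrees of freedom. No new data or visits are needed.

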### Monitoring

No data monitoring committee will be employed, given the low-risk nature of the intervention examined. Subsequently, no independent auditing will occur throughout the trial.

## Ethics and dissemination

### Research ethics approval

Ethics approval was provided by the Deakin University Human Research Ethics Committee (ID: 2022-162) on 26 September 2022.

### Protocol amendments

Any protocol amendments will be communicated via updates to the Australian New Zealand Clinical Trials Registry (ACTRN12622001276741). A section on protocol amendments will also be included in any publications from this work.

### Consent

All potential participants will be screened initially via phone with a research team member to determine their eligibility. All eligible participants will be required to provide informed consent on reviewing the participant information and consent form (online supplemental appendix D). Participants will retain a copy of the forms, including information regarding their ability to withdraw their consent if desired. This consent process will be uniform across all participants. The right to withdraw consent without question or consequence is outlined in the patient information and consent form, which will be provided to patients electronically before and once again after enrolment.

### Confidentiality

Each participant will be allocated a study-specific code. However, all data will remain reidentifiable for cross-checking data entry and disseminating individual data to participants after the study. The codes will be stored electronically on password protected servers at the involved institutions, and only research staff involved in this project will have access. The codes will be kept separate from personal data collected on the participants.

### Ancillary and post-trial care

On completion of the 12-week study, participants in the waitlist control will be offered the study intervention under the supervision of the study team. No other follow-up is currently planned beyond the 12-week study period.

### Dissemination policy

Authorship of outputs from this research will be in line with the International Committee of Medical Journal Editors guidelines. Findings from the primary outcomes of this study will be reported in journal articles and student theses, which will include results regardless of the direction or magnitude of the effect. The results will also be presented at leading national and international conferences, clinical forums and to other relevant health professionals and stakeholders and the participants. The dissemination of research results will only consist of aggregated data; individual participants will not be identified. All participants will be able to elect to receive a brief report of their study results via email after the study. If the participant expresses interest in the study results, they can request to have a copy of published articles sent to them.

## Discussion

This will be the first study to evaluate whether running exercise can improve IVD health. Surgical options are commonly implemented to treat poor IVD health yet are associated with additional risk. Therefore, identifying conservative options to improve IVD health has the potential to reduce the marked burden of LBP.

## Data Availability

Data sharing not applicable as no datasets generated and/or analysed for this study. Protocol only.
